### Data Management

All data gathered throughout the study will be entered directly into the REDCap system. Upon enrollment, participants will be assigned a unique subject number for identification purposes within the survey. Access to the REDCap program, where all data will be securely stored, will be limited to authorized study personnel.

The principal investigator (MT) and primary statistician ([name]) remain blinded to the randomization of participants across the study arms throughout the protocol. Other designated study staff will have access to this information for specific tasks such as recruitment, obtaining consent, conducting orientation and welcome calls, coaching sessions, and managing the shipment of intervention packages.

We will also perform data verification, including confirming the completion of surveys, questionnaires, and the accurate recording of HbA_1c_ values. Given that this project is a pilot feasibility and efficacy study with a duration of 6 months and is deemed to have minimal risks, a data monitoring committee is unnecessary. The principal investigator (MT) holds responsibility for maintaining protocol fidelity and overseeing data collection procedures throughout the study period.

### Analyses

#### Statistical Analysis

Descriptive statistics will be prepared to show the sample statistics and analyzed separately for baseline and 6-month postproject. Paired 2-tailed *t* tests and chi-square tests will be used to assess the change in continuous and discrete outcomes from baseline to 6 months for each arm. Furthermore, within-group differences will be assessed using 2-tailed *t* tests (paired and unpaired) and chi-square tests.

Multivariate linear mixed models will be used to assess repeated measures with continuous outcomes, assess the joint effects of baseline measures on 6-month outcomes, and account for the correlation between repeated measures. Quality control analyses will be performed, including assumption checking, estimating descriptive statistics of participant attrition and overall instrument completion, and investigating missingness patterns. Key variables at baseline will be examined to evaluate whether there is any systematic variation between the study groups. A participant who no longer participates in study activities will be considered lost to follow-up. App analytics on key performance indicators will be used for participants who are lost to follow-up. We anticipate the loss to follow-up rate to be approximately 20%. The primary analysis will follow the intention-to-treat principle, including all participants as originally assigned regardless of adherence. Secondary or compliance analyses will be considered if appropriate.

All qualitative data collected in the study will be content analyzed using NVivo (Lumivero), a qualitative data analysis software [48], including qualitative data collected for the feasibility, acceptability, and fidelity of interviews and meeting notes. The steps for content analysis include (1) transcribing audio recordings, (2) checking transcription against recordings for accuracy, (3) developing coding categories, (4) assigning codes to text, and (5) reviewing coded data to identify themes across the dataset.

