### Sample Size

In total, 90 participants will be enrolled, divided into 3 groups of 30 participants each (low-technology, high-technology, and attention control). The sample size is determined based on the primary use of analysis of covariance and uses a 2-sided test with a type I error rate of 0.05. An intention-to-treat analysis and multiple imputations are incorporated. Given a minimum correlation of 0.7 between the baseline and follow-up outcomes, there will be an 80% chance of detecting an effect size of 0.65.

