Given that self-management is crucial in managing T2D and also considering that persons with disabilities face barriers that prevent them from successfully managing their diabetes, a study looking to create an available, inclusive, and accessible diabetes management program for people with disabilities is important. To the best of our knowledge, there is no existing program in the United States explicitly providing remote DSME and MNT tailored for persons living with disabilities.

This study has limitations. Factors such as the supportive group setting, the instructor, or individual components of the program may influence health outcomes in different ways. To account for potential confounding factors, we have chosen a randomized design. Additionally, behavior changes, such as participating in an organized intervention, could contribute to improvements, including adopting healthier diets. As with any complex intervention, various factors may impact the outcomes. However, this reflects real-world clinical scenarios. Using a randomized design, the study aims to minimize the influence of confounding variables and provide more reliable findings. Additionally, several aspects of our trial design may pose potential limitations. First, participants with mobility limitations or accessibility issues may be unable to visit the contracted laboratory for their HbA_1c_ test and instead self-report their HbA_1c_ levels. These self-reported data may not be entirely accurate or up to date. Additionally, as the study is conducted remotely, some participants, particularly older individuals, may face technical challenges, such as difficulty navigating the platform or accessing the intervention materials.

That notwithstanding, this study has some strengths. To begin with, the methodological strengths of the study include the randomized controlled design, preregistration in a clinical trials registry, the inclusion of make-up and follow-up classes, and the use of both quantitative and qualitative measures. Another strength is a third-party testing company’s involvement in the HbA_1c_ tests, ensuring impartiality and reliability in the results.

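### The Statistical Analysis section does not carry through the ANCOVA that sized the trial, names no between-arm contrast or test, and assigns unpaired tests to within-group differences

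*Protocol article*

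**What the plan says.** All references are to the protocol article.

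- **Sample Size:** "The sample size is determined based on the primary use of analysis of covariance"; the calculation "uses a 2-sided test with a type I error rate of 0.05". It continues: "Given a minimum correlation of 0.7 between the baseline and follow-up outcomes", "there will be an 80% chance of detecting an effect size of 0.65". Enrolment is 90, or 30 per arm.
- **Statistical Analysis, first test sentence:** it opens with paired t tests, then reads "chi-square tests will be used to assess the change in continuous and discrete outcomes from baseline to 6 months for each arm".
- **Statistical Analysis, second test sentence:** for within-group differences it lists two-tailed "tests (paired and unpaired) and chi-square tests".
- **Statistical Analysis, mixed model:** multivariate linear mixed models are planned for continuous outcomes, to relate baseline measures to 6-month outcomes and "account for the correlation between repeated measures". The sentence names no arm term and no arm-by-time contrast. The section refers to a primary analysis by intention to treat without saying which method that is. About 20% loss to follow-up is expected.
- **Abstract:** the mixed models are said to relate level of technology to the outcomes. The primary outcome is the proportion in each group whose self-management improves.
- **Introduction (last paragraph) and Results:** the hypotheses compare arms.
- **Study Design:** every arm receives the same classes, in quality and quantity.

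**The concern.** Two sections of one article disagree on the main analysis. The trial is sized on a baseline-adjusted comparison of arms. The analysis section then names only tests of change inside an arm, plus a model whose arm comparison has to be inferred from the Abstract. The proportion called primary has no between-arm test: the chi-square tests are described as within-arm, and the mixed models are for continuous outcomes.

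The second test sentence is also wrong on either reading. Baseline and 6-month values come from the same people, so an unpaired test of within-group change uses the wrong standard error. If the authors meant between-group, the test is valid but drops the baseline adjustment that the power statement assumes.

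At stake is what may be reported as the main result. Because all arms are taught the same classes, all may improve. A significant change in one arm and not in another says little about the difference between them, and the text does not rule out that comparison.

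**Working it through.** **Inputs.** From Sample Size: correlation r = 0.7, effect d = 0.65, two-sided alpha 0.05, n = 30 per arm. From Statistical Analysis: 20% loss, so 30 × 0.8 = 24 per arm. Assumed here: normal outcomes with SD 1 at both times, and d in SD units for a pairwise contrast, since the article states neither the scale nor the contrast.

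**1. The plan's own figure.** ANCOVA residual SD = √(1 − 0.7²) = 0.714.
- 30 per arm: SE = 0.714 × √(2/30) = 0.184; 0.65/0.184 = 3.53; power = Φ(3.53 − 1.96) = 94% (93% with the t distribution).
- 24 per arm: SE = 0.206; 0.65/0.206 = 3.15; power = 88% (87% with t).

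The stated 80% does not follow from the stated inputs alone. Values close to it need unstated choices: an omnibus three-arm F test at 24 per arm with means 0, 0.325 and 0.65 gives 79.4%; a pairwise test at alpha 0.025 and 24 per arm gives 80.3%. The statement is conservative for a pairwise ANCOVA, and the present point does not depend on it.

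**2. Unpaired t test read literally (within one arm).** The true variance of the mean change is 2(1 − r)/n = 0.6/n. The unpaired test uses 2/n. SE ratio = √(2/0.6) = 1.83, so the test rejects only when the correctly scaled statistic passes 1.96 × 1.83 = 3.58. The large-sample type I error is about 0.03%. Simulation gives 0.07% to 0.1% at 24 to 30 per arm and about 0.2% at 9 per arm. Simulated power for a true change of 0.4 SD is 23% against 79% for the paired test (30 per arm), and 15% against 68% (24 per arm).

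**3. Unpaired t test read as between-group.** SE = √(2/30) = 0.258; 0.65/0.258 = 2.52; power = Φ(2.52 − 1.96) = 71%, or 70% with t. This compares with 93% (t) for ANCOVA.

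**4. Independent-sample chi-square on paired binary data.** For an outcome cut at the mean with r = 0.7, simulated type I error is about 0.6% to 1%, not 5%.

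**5. What within-arm p-values would show.** Change SD = √(2 × 0.3) = 0.775. Suppose two arms improve equally, so there is no arm difference. With p the power of one paired test, exactly one of the two arms is significant with probability 2p(1 − p).

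| Common improvement (assumed) | 30 per arm | 24 per arm |
|---|---|---|
| 0.3 SD | 50% | 50% |
| 0.4 SD | 34% | 43% |
| 0.5 SD | 13% | 25% |

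For example, at 0.5 SD and 24 per arm p = 0.857, and 2 × 0.857 × 0.143 = 0.245. These rates apply only if someone reads arm differences from within-arm results.

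**The case against.** The strongest reply is the mixed model. The Abstract says it relates technology level, which is the arm, to the outcomes. With a baseline term and an arm contrast it would be close to ANCOVA for continuous outcomes and lose little precision. A reader might infer that the trial has no between-arm analysis, or that arms will be compared by setting within-arm p-values side by side. The documents support neither: a between-arm model is planned, and no section announces that comparison. This part of the reply stands. It does not supply the missing arm contrast in the analysis section, the link to the sample-size method, or a test for the proportion.

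On the named tests, the first sentence opens with paired t tests, which are right for continuous change. Chi-square could cover McNemar's test, which a condensed article need not name. Within-group is probably a slip for between-group, since the preceding sentence already covers change in each arm. Read literally, the error is conservative: it loses power and does not create false positives. All of this is fair, but the sentence still needs correcting, because the slip reading leaves an unadjusted test.

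A reader might also infer that shared classes inflate the type I error. Study Design describes class cohorts, and the Discussion says "Factors such as the supportive group setting, the instructor, or individual components of the program may influence health outcomes in different ways". But participants are randomised individually, the article does not say whether a cohort held one arm or several, and it gives no intraclass correlation. No inflation can be claimed from these documents.

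**Conclusion.** The point holds as a mismatch inside the article and as an error in one sentence. The method that sized the trial is absent from the analysis section; the tests named there are within-arm although the hypotheses are between-arm; the arm contrast of the mixed model is left to the Abstract; and the proportion named as primary has no between-arm test. The unpaired wording is wrong as written. Taken literally, it gives a type I error near 0.1% in place of 5%; taken as between-group, 70% power in place of 93% at 30 per arm. These sizes rest on the article's r = 0.7 and d = 0.65, with normal outcomes and d read as a pairwise difference in SD units. The chi-square figure also assumes an independent-sample test and a cut at the mean.

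Because a between-arm model is already planned, this is something that should be fixed, not a failure of the whole analysis.

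**What to change.** In Statistical Analysis:

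1. Name one primary between-arm analysis adjusted for baseline: either ANCOVA of the 6-month score on arm and baseline score, or the planned mixed model with an explicit arm contrast at 6 months. Report between-arm differences with 95% confidence intervals. State its relation to the other method, so that Sample Size, Statistical Analysis and the Abstract agree.
2. Add a between-arm comparison of the proportion improved, since the Abstract makes this the primary outcome.
3. Correct the sentence that assigns unpaired tests to within-group differences.
4. Specify McNemar's test for any paired binary change.
5. Report within-arm change descriptively (mean change, 95% confidence interval) and state that it does not support arm comparisons.

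Adjustment for class cohort can be an optional sensitivity analysis.

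The cost is wording, to be settled before the analysis planned for fall 2025, and the loss of within-arm p-values. No extra participants are needed: pairwise ANCOVA at effect 0.65 has about 87% power with 24 completers per arm. That holds for the planned 90. The Recruitment and Results sections report 28 enrolled, about 9 per arm, where the same calculation gives about 50%; that discrepancy is a separate matter.

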#### Qualitative Analysis

Moreover, the study will include qualitative interviews conducted after the intervention to evaluate the program thoroughly. These interviews aim to assess the intervention’s effectiveness as a feasible approach for managing diabetes. Multimedia Appendix 3 shows the interview guide. The interviews will be transcribed and analyzed using an inductive content analysis method as described by Elo and Kyngäs [49]. The analysis will be performed in 3 phases. The first phase is open coding, followed by creating categories and abstraction [49]. NVivo software will be used to facilitate the organization and analysis of the qualitative data.

### Data Monitoring

Any personal information collected during the study, including demographic details and other sensitive data, will be gathered and stored in compliance with the HIPAA regulations using the secure REDCap platform. Access to this confidential information will be limited to authorized study staff who have received approvals. The storage and handling of personal data will adhere to the guidelines, oversight provided by the university’s IRB, and the policies established by affiliated entities. The laboratory testing service will manage the collection and processing of blood samples for HbA_1c_ testing. Study personnel will not handle or have access to the blood samples at the testing laboratory.

### Harms

This study will track and evaluate all adverse events. These events will be assessed for their severity and potential causality. Any identified adverse events will be reported to the IRB and other pertinent regulatory bodies, as required by the study protocols and ethical guidelines.

### Auditing

The study protocol will undergo regular evaluations at specified intervals, such as weekly, monthly, or quarterly, to ensure adherence to the study’s design and consistent implementation. Auditing procedures will encompass various elements, including checklists, coaching call logs, audio recordings or coaching calls, content resource banks, telehealth platform reviews, and event logs; review of participant food, physical activity, medication, glucose entries, and time spent on the platform; and team meetings to discuss participant progress and protocol adherence.

## Results

We hypothesize that participants in the high- or low-technology intervention groups will show improvements in self-management behaviors related to T2D and self-efficacy compared to the control group at the 6-month follow-up. Again, we hypothesize that the high-technology intervention arm will result in better outcomes regarding reductions in HbA_1c_ than the low-technology and control arms. Additionally, we also hypothesize that the YumABLE intervention is feasible and acceptable to adults with permanent physical disability and T2D and that fidelity to the program will be maintained.

The development of the telehealth platform, which includes the dashboard and educational content, along with the creation of the landing website, has been completed by the study’s technical support team. In addition, research personnel have developed the database using REDCap to serve as the storage for data and communication tools such as emails and text notifications. The study began in June 2024. Since June 2024, intervention materials have been finalized, the IRB submissions have been completed, and participant recruitment began. In total, 28 participants have been enrolled and received the MNT and DSME remote class. Recruitment has ended, and we anticipate completing data collection by August 2025. Make-up classes were delivered to participants in any of the 3 cohorts between November 2024 and December 2024. The final 3-month follow-up classes were held for each cohort 3 months after the first class and were completed in February 2025. Data will be analyzed in fall 2025. Manuscript preparation and dissemination of study results are planned for spring 2026.

## Discussion

Previous research has showed that comprehensive diabetes education is required to equip patients with the necessary self-management skills needed to manage the condition. Likewise, diabetes education has been found to improve patient knowledge, improve diabetes control, and delay complications [50-56]. The American Diabetes Association has pointed diabetes education as the cornerstone therapy for the patient with diabetes [54].

Numerous publications have highlighted the importance of technology in diabetes care and management [34,35,57]. Sharma et al [57] posit that technology use in providing diabetes education leads to improved patient access and clinical outcomes, reduces the cost of care, and addresses gaps in care. Patients with diabetes who get live telephone coaching for a specified duration can gain advantages from consistent health status monitoring, leading to enhanced self-efficacy, improved health outcomes, and decreased hospitalization rates, surgical expenses, and total health care expenditures [58-61]. The reduction of HbA_1c_ levels has been a notable benefit achieved by telephonic support [60].

Likewise, web-based education is an effective tool for promoting diabetes self-management. Some websites exclusively provide diabetes-related content and resources, while others include an opportunity to interact with a coach [62]. Other websites provide digital record-keeping tools that enable patients to track and monitor their food and physical activity as well as generate reports or logs [63]. Moreover, other websites include blogs, healthful recipes, menus, and holiday meal planning assistance [57]. Some clinical web-based supportive educational tools include remote chatting, discussion forums, emailing choices, and the ability to contact a live diabetes coach [57]. Indeed, web-based educational interventions have shown promise in supporting diabetes self-management. Such digital training approaches have been linked to enhanced treatment adherence and improved health indicators, highlighting their potential as effective tools in early diabetes care [63].

Given that self-management is crucial in managing T2D and also considering that persons with disabilities face barriers that prevent them from successfully managing their diabetes, a study looking to create an available, inclusive, and accessible diabetes management program for people with disabilities is important. To the best of our knowledge, there is no existing program in the United States explicitly providing remote DSME and MNT tailored for persons living with disabilities.

This study has limitations. Factors such as the supportive group setting, the instructor, or individual components of the program may influence health outcomes in different ways. To account for potential confounding factors, we have chosen a randomized design. Additionally, behavior changes, such as participating in an organized intervention, could contribute to improvements, including adopting healthier diets. As with any complex intervention, various factors may impact the outcomes. However, this reflects real-world clinical scenarios. Using a randomized design, the study aims to minimize the influence of confounding variables and provide more reliable findings. Additionally, several aspects of our trial design may pose potential limitations. First, participants with mobility limitations or accessibility issues may be unable to visit the contracted laboratory for their HbA_1c_ test and instead self-report their HbA_1c_ levels. These self-reported data may not be entirely accurate or up to date. Additionally, as the study is conducted remotely, some participants, particularly older individuals, may face technical challenges, such as difficulty navigating the platform or accessing the intervention materials.

That notwithstanding, this study has some strengths. To begin with, the methodological strengths of the study include the randomized controlled design, preregistration in a clinical trials registry, the inclusion of make-up and follow-up classes, and the use of both quantitative and qualitative measures. Another strength is a third-party testing company’s involvement in the HbA_1c_ tests, ensuring impartiality and reliability in the results.

The results from this study will expand our understanding of how technology-delivered behavioral interventions can effectively address the challenges of managing diabetes, particularly among individuals with permanent physical disabilities and their families. A combined approach of DSME and technology offers a promising, easily accessible, and engaging intervention that may serve as a practical pathway for improving diabetes management.

This study provides future directions. First, it can lead to more studies on how artificial intelligence could be used in the delivery of diabetes education among individuals with various forms of disabilities. In addition, the study can help provide insight regarding an effective approach to combine more than 1 technology in providing diabetes management education.

We intend to present study findings at diabetes, endocrinology, and digital health conferences and submit the data for publication in peer-reviewed open-access publications. In addition, we will consult with health care leaders and diabetes care teams within our health system on potential changes to diabetes education methods and digital intervention protocols.

In conclusion, this randomized controlled study, with an anticipated 90 participants, will explore the effects of combined DSME and technology among individuals with diabetes and a permanent physical disability. The primary aim is to assess how technology-enhanced DSME influences diabetes management. The findings from this intervention study could offer valuable insights for health care professionals, health educators, and public health personnel, informing future strategies for managing diabetes in individuals with physical disabilities and more broadly among all persons living with T2D.

